# 5 Design

## 5.1 Overall design

This study was a single-center, prospective, randomized (1: 1) clinical trial. The comparison of live birth rates between sustained release vaginal progesterone gel and intramuscular progesterone in hormone replacement FET cycles was carried out. 1500 patients were recruited and randomly divided into two groups. Patients in group A were received sustained release vaginal progesterone gel and in group B received intramuscular progesterone.

## 5.2 Randomization

1. Personnel who are not involved in this study operated computer to generate random allocation table and 1500 random numbers were randomly divided into two groups in the proportion of 1:1 (for example: random number 1, group A, sustained release vaginal progesterone gel group).

2. After the confirmation of patients involved in the study, investigator operated computer to generate random number on the day of endometrial secretory transformation in hormone replacement FET cycles and the group that patients belonging to was found in the random allocation table. Patients in group A were received sustained release vaginal progesterone gel and in group B received intramuscular progesterone.

3. Both investigator and patients knew the grouping situation on the day of endometrial secretory transformation. For each visit, investigator will inform the patients how to administrate medicine and next visit date.

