# 6 Subjects selection

Inclusion criteria:

1. Date from September 1^st^, 2010 to January 31^st^, 2013
2. Hormone replacement FET cycles;
3. Subjects with age ≥20 and ≤40 years old;
4. With d3 frozen embryos;
5. Endometrial thickness ≥7mm on the day of secretory transformation;
6. Agreed to sign informed consent form。

Exclusion criteria were in hormone replacement FET cycles

1. Patients with uterine disorders, such as uterine malformations (unicornuate uterus, bicornuate uterus, mediastinal uterus, double uterus), adenomyosis, submucosal fibroids and intrauterine adhesion;
2. Suffered 3 or more spontaneous abortions (including biochemical pregnancy);
3. Embryo transfer in patients failed for 3 or more times (including biochemical pregnancy);
4. Patients not suitable for assisted reproductive technology;
5. Patients that were taking medication or treatment having influence on reproductive and metabolic function, including diabetes drugs, anti-hypertensive drugs (diazoxide, ACEI inhibitors, calcium channel blockers), Chinese herbal medicine and acupuncture;
6. Endometrial thickness <7mm on the day of secretory transformation;
7. Patients who can’t comply with the study protocol.

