**Randomized grouping**

1. Whether or not the patient complies with the random grouping conditions？□ Yes □ No

2. Whether or not the patient agrees to be randomly grouped？□ Yes □ No

3.Date of Randomization：__ ____ __/__ __/__ __（Y/M/D）

4. The patient will be randomly assigned to：

□Group A（sustained release vaginal progesterone gel group）□Group B（Intramuscular progesterone group）

Research Program：A comparison of live birth rates between sustained release vaginal progesterone gel and intramuscular injection of progesterone in hormone replacement frozen-thawed embryo transfer cycles:

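### Section 5.2 does not secure allocation concealment: the investigator draws the random number, the holder of the allocation table is not named, and the draw is not logged

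*Combined protocol and SAP*

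**What the plan says.** Section 5.2 sets out three steps.

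- **Table.** "Personnel who are not involved in this study operated computer to generate random allocation table". In it, "1500 random numbers were randomly divided into two groups in the proportion of 1:1". The example given ties number 1 directly to group A, so anyone holding the table can convert a number into an arm.
- **Draw.** "After the confirmation of patients involved in the study", the "investigator operated computer to generate random number on the day of endometrial secretory transformation". Then "the group that patients belonging to was found in the random allocation table". The investigator is the only actor named in this step. Who holds the table and who looks up the arm are not stated.
- **Knowledge of the arm.** "Both investigator and patients knew the grouping situation on the day of endometrial secretory transformation".

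Section 4.3 places the endometrial thickness exclusion and the random allocation at the same visit. On CRF page 6 the thickness check comes first. The randomised-grouping items follow: eligibility, the question "Whether or not the patient agrees to be randomly grouped", the date of randomisation, and the arm. The page has no field for the random number or for the time of the draw.

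The documents mention no sealed envelopes, no telephone or central release, no custodian of the table, no lock on a number once drawn and no log of draws.

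**The concern.** Independent generation protects how the sequence is made. It does not keep the arm from the person enrolling until entry is irrevocable, and that second protection is what prevents selection.

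If the person who draws the number can also read the table, two things can happen without leaving a trace. A number that gives an unwelcome arm can be drawn again, or a woman can be left out after her arm is seen and before anything is recorded. The CRF does not hold the number, so neither event could be found later from the trial records. The intention-to-treat principle in Section 11.2 does not help, because it covers only recorded allocations.

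The setting makes this more than theoretical. The treatments are a daily injection and a vaginal gel, and neither investigator nor patient is blinded. The Background lists drawbacks of the injection, and Section 11.1 assumes that gel does better by 10 percentage points. By day 0 the investigator knows the woman's age, her pregnancy and transfer history and her endometrial thickness, all plausibly related to live birth. The planned tests in Section 11.2 (chi-square and t) include no adjustment for such factors.

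**Working it through.** **The plan's own figure.** Section 11.1 gives rates of 0.40 and 0.30, α = 0.01 and power 0.90. With a two-sided test and pooled variance:

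n = [2.576·√(2·0.35·0.65) + 1.282·√(0.40·0.60 + 0.30·0.70)]² / 0.10² ≈ 675 per group.

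675 / 0.90 = 750 per group. Both stated figures reproduce. Section 11.1 does not give sidedness, but a one-sided test would need 590, so two-sided is taken as intended. The sample size is not in question and does not change.

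**How large could the effect be?** The documents give no steering rate and no spread of prognosis. These inputs are assumptions:

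- no true treatment effect;
- half the women with a 45% chance of live birth and half with 25% (mean 35%, the midpoint of the planned rates);
- a fraction f of assignments made by prognosis (better prognosis to one arm, poorer to the other) and the rest at random;
- 750 women per arm, all analysed.

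The favoured arm then holds a share 0.5 + f/2 of better-prognosis women, and the other arm 0.5 − f/2. The spurious difference is

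d = f × (0.45 − 0.25) = 0.20·f.

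The standard error under the null is √(2·0.35·0.65/750) = 0.0246, so the two-sided 1% test rejects beyond ±2.576 × 0.0246 = ±0.0634.

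For f = 10%, the arms have rates of 0.36 and 0.34, so d = 0.02. The upper-tail deviate is (0.0634 − 0.02)/0.0246 ≈ 1.76, a probability of about 3.9%. The lower tail adds less than 0.1%.

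| Assignments steered | Spurious difference | Error of nominal 1% test | Error of nominal 5% test |
|---|---|---|---|
| 2% | 0.4 points | 1.1% | 5.3% |
| 5% | 1 point | 1.6% | 6.9% |
| 10% | 2 points | 3.9% | 12.8% |
| 20% | 4 points | 17% | 36.9% |

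Half of the steered women would have reached the same arm by chance. A 10% rate (150 of 1500) therefore means about 75 women whose arm was actually changed. The table models redrawing. Non-entry after the draw would work in the same direction, but its size depends on who is left out, and nothing in the documents allows that to be quantified.

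**The case against.** The case for the plan has substance.

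- **The lookup is in the passive voice.** A reader might infer that the investigator reads the table and that allocation is therefore unconcealed. The documents do not say who does the lookup. What they support is that concealment is neither described nor secured.
- **The order is right.** A reader might infer that the investigator can see the arm before deciding on eligibility. Section 5.2 puts the draw after confirmation of the patient, and CRF page 6 puts thickness, eligibility and agreement before the arm. A freshly drawn number is also harder to anticipate than a list read in order. This stands, and it narrows the exposure to what can happen after the draw.
- **The compliance exclusion.** Section 6 excludes women unable to "comply with the study protocol", which might look like a discretionary way out on day 0. It appears neither in the CRF exclusion list nor in the pre-randomisation check on page 6, which lists only thickness, a measured value. The documents do not show it being used at that point.
- **Repeated numbers.** A reader might infer that drawn numbers can recur and upset the 1:1 split. The plan does not say how numbers are drawn. Even if they could recur, the result would be simple randomisation, with a standard deviation of √(1500·0.25) ≈ 19 in the size of an arm. That causes no bias and hardly affects power.
- **Motive.** A preference for gel or injection biases live birth only if steering follows prognosis. At 2% to 5% steering, the 1% error barely moves.

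None of this supplies the missing safeguard. No custodian, lock or log is described, and the CRF cannot show whether the first number drawn was the one used. Live birth is a fairly objective endpoint, but that does not protect against unequal entry.

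**Conclusion.** The point holds as a gap in a stated procedure. Followed as written, Section 5.2 permits an untraceable redraw, or non-entry after the arm is seen, in an open-label trial. The documents establish exposure only. They do not show that any draw was repeated or any woman dropped, and open-label treatment does not itself cause selection bias.

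The possible size runs from negligible to serious. On the assumed 45%/25% prognosis split, the nominal 1% error ranges from about 1.1% (2% steered) to about 17% (20% steered). These figures illustrate and do not estimate. A wider or narrower split changes them in proportion through d = 0.20·f.

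The gap should be closed, because the comparison rests on concealment. An audit of draws or a look at baseline balance might detect some steering, but would not reliably remove it.

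**What to change.** Rewrite Section 5.2, item 2:

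1. The outside personnel who generate the table also prepare consecutively numbered, opaque, sealed envelopes, or load a locked computer release. The investigator has no access to the table and no longer generates a number.
2. Each allocation is opened in strict sequence, only after the eligibility and agreement items on CRF page 6 are completed and signed.
3. CRF page 6 gains fields for the allocation number and the time of opening.
4. Every opened allocation counts in the intention-to-treat set, whether or not treatment or transfer follows.

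The cost is one rewritten paragraph, two CRF fields, a single round of envelope preparation or system set-up, and a few minutes per randomisation. Preparing the envelopes is an added task for the outside personnel, but not a standing role.

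Section 10 ends recruitment on 31 January 2013. If recruitment is already complete, the procedure cannot be changed. The sponsor should then state who held the table and how the arm was withheld, reconcile whatever record of draws exists against the table, and report baseline balance by arm.

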## 5.3 Protocol of frozen embryo hormone replacement

Estradiol valerate (Progynova, Germany Bayer) 4mg/d, orally, was administrated on day 3 of menstruation for 10 days. 10 days after administration, B-mode ultrasound examination was conducted. If endometrial thickness <7 mm, increasing the dose of estradiol valerate to 6-8 mg/d. If endometrial thickness was ≥ 7 mm, progesterone would be administrated to promote endometrium to secretory phase.

## 5.4 Endometrial secretory transformation and luteal phase support

Group A: On the day of endometrial secretory transformation (D0), patients were administrated sustained release vaginal progesterone gel 90mg/d, dydrogesterone 20mg/d orally and estradiol valerate 4-8 mg/d. Embryo with top score on D3 FET was administrated at the same dose continually to the 14 days after transfer. The number of transferred embryos was defined in accordance with standards of Ministry of Health. For subjects <35 years old with first embryo transfer, 2 embryos were allowed to transfer at most; for subjects ≥ 35 years old or with re-transfer, 2-3 embryos were allowed.

Group B: On the day of endometrial secretory transformation (D0), patients were administrated intramuscular progesterone 40 mg/d, dydrogesterone 20mg/d orally and estradiol valerate 4-8 mg/d. Embryo with top score on D3 FET was administrated at the same dose continually to the 14 days after transfer. The number of transferred embryos was defined in accordance with standards of Ministry of Health. For subjects <35 years old with first embryo transfer, 2 embryos were allowed to transfer at most; for subjects ≥ 35 years old or with re-transfer, 2-3 embryos were allowed.

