## 4.4 Visit on the day of embryo transfer

The information of embryos transfer was recorded and the corresponding form was completed. Patients were asked whether any adverse events had occurred, if any, adverse event reporting form should be completed.

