**Inspection Visit Form for Embryo Transfer Date** **(page 7)**

**Frozen-thawed** **embryo transfer**

1. Endometrial thickness before transfer：mm；

2. The number of embryos transfer：______

3. The number of remaining frozen-thawed embryos：______

4. Day-old of remaining frozen-thawed embryos：

□D3 □D5

5. Reasons for not-performed embryo transfer：

□Thaw failure of embryos，no available embryo transfer

□Uterine factor

□Others

Research Program：A comparison of live birth rates between sustained release vaginal progesterone gel and intramuscular injection of progesterone in hormone replacement frozen-thawed embryo transfer cycles:

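### Nothing requires the number of embryos to be fixed before the open allocation is known, so the choice within the permitted range can be influenced by the arm

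*Combined protocol and SAP*

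**What the plan says.** **Allocation.** Section 5.2 places randomisation on D0: "investigator operated computer to generate random number on the day of endometrial secretory transformation in hormone replacement FET cycles". It is open from that moment: "Both investigator and patients knew the grouping situation on the day of endometrial secretory transformation".

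**Number of embryos.** Section 5.4 gives the same rule, in the same words, for both groups. It refers to an outside standard, "The number of transferred embryos was defined in accordance with standards of Ministry of Health", and reproduces limits only. The first is "For subjects <35 years old with first embryo transfer, 2 embryos were allowed to transfer at most"; the second is "for subjects ≥ 35 years old or with re-transfer, 2-3 embryos were allowed". It does not say how to choose within either limit, who chooses, or when. Section 6 admits women aged 20 to 40 and excludes those with three or more failed transfers, so both routes into the wider range (age 35 or over, and re-transfer) are open.

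**Recording.** Section 4.4 covers the transfer visit: "The information of embryos transfer was recorded and the corresponding form was completed". The field "The number of embryos transfer" is on case report form page 7, the transfer-day form. Page 6, completed on D0 and containing the randomisation block, has no field for a planned number. Page 7 asks for a reason only when no transfer takes place.

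**Outcome and analysis.** Live birth rate is primary, and implantation rate is a secondary outcome (sections 5.6 and 9). Section 11.2 compares proportions with a chi-square test and mentions no stratification or adjustment.

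**The concern.** Randomisation balances what is settled before it. A treatment decision taken later, by people who know the arm, is not protected. Here that decision is how many embryos to transfer, which can plausibly affect live birth, implantation and multiple pregnancy by a route other than progesterone.

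The plan itself supplies a reason for expecting the arms to differ. Section 11.1 assumes 40% live birth with gel and 30% with intramuscular progesterone, and section 12.1 tells patients that the effect in their group may be worse than in the other. A clinician or patient who holds either view could compensate, even without intending to, within the two-to-three range.

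Analysis cannot cleanly repair this. The number actually transferred is itself post-randomisation, so adjusting for it does not restore the randomised comparison. Nor can page 7 as it stands distinguish a number changed by thaw loss from one changed because of the arm.

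**Working it through.** **1. Order of events.** Consent and screening come first, then D0 with randomisation and disclosure (section 5.2; form page 6), then transfer and the first record of embryo number (section 4.4; form page 7). No section states when the number is chosen, and none requires it to be settled before disclosure. The gap is therefore a missing safeguard; a post-allocation choice is possible but not documented.

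**2. The plan's own sample size.** Inputs from section 11.1: rates 0.40 and 0.30, alpha 0.01, power 0.90, ratio 1:1. Sidedness is not stated; two-sided is taken because it reproduces the figure. With pooled variance and no continuity correction:

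n = [2.576 × √(2 × 0.35 × 0.65) + 1.282 × √(0.40 × 0.60 + 0.30 × 0.70)]² / 0.10² = 675 per group (rounded up).

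Inflated for 10% dropout: 675 / 0.90 = 750. Both agree with the plan.

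**3. Size of a possible bias.** Bias in the live-birth difference = f × d × e. None of the three factors is given in the documents; all are assumptions.

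| Factor | Meaning | Assumed range |
|---|---|---|
| f | share of women eligible for two or three embryos | 30-70% |
| d | difference between arms, among those women, in the share given three | 10-30 points |
| e | gain in live birth from a third embryo | 5-10 points |

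- Lowest: 0.30 × 0.10 × 0.05 = 0.0015, or 0.15 points.
- Highest: 0.70 × 0.30 × 0.10 = 0.021, or 2.1 points.
- A case between: 0.50 × 0.20 × 0.10 = 0.010, or 1.0 point.

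**4. False-positive rate if the arms are truly equal.** Take a 35% live birth rate (midway between the plan's two rates) and 675 per arm: SE = √(2 × 0.35 × 0.65 / 675) = 0.0260. With shift k = bias / SE, the rejection rate at two-sided 0.01 is Φ(k − 2.576) + Φ(−k − 2.576).

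| Bias (points) | k | False-positive rate |
|---|---|---|
| 0.15 | 0.06 | 1.0% |
| 1.0 | 0.39 | 1.6% |
| 2.1 | 0.81 | 3.9% |

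With a null rate of 30% the last figure is 4.1%, so the base rate matters little.

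**5. Power if the bias opposes a true 40% v 30% difference.** Replace 0.40 by 0.40 minus the bias, with 675 per arm and alpha 0.01.

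| Bias (points) | Rates compared | Power |
|---|---|---|
| 0 | 40.0% v 30% | 90.0% |
| 0.15 | 39.85% v 30% | 89.0% |
| 1.0 | 39.0% v 30% | 81.8% |
| 2.1 | 37.9% v 30% | 68.8% |

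**The case against.** **Timing.** A reader might infer that the number is in fact decided after allocation, on the transfer day. The documents do not say so. Sections 4.4 and 5.4 and form page 7 show when the transfer is recorded, not when the decision is made. What stands is that no prior decision is required.

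**Imbalance.** A reader might also infer that the arms will differ in embryo number. The limits are identical in both arms and no imbalance is shown. A firm belief about which arm is weaker is not documented either: section 11.1 assumes a gel advantage, while section 2 reports no significant difference in fresh cycles. This objection stands, and it is why the bias is potential and its direction unknown.

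**Size.** A larger figure is tempting. A 3-point bias tested at alpha 0.05 would give a false-positive rate of about 21%. That alpha is not the plan's. With a 10-point embryo effect, a 3-point bias also needs a 30-point imbalance across whole arms, although only women aged 35 or over or with a re-transfer may receive three. If half are eligible, the gap among them would have to be 0.30 / 0.50 = 60 points; if 30% are eligible, 100 points. At the low end the effect is almost nil. The documents also do not quantify how strongly embryo number drives live birth.

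**False positives or lost power.** If clinicians shared the plan's expectation and compensated in the intramuscular arm, the bias would work against the hypothesised gel advantage. Lost power is then at least as relevant as a false positive.

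**Existing safeguards.** The actual number is collected and can be reported by arm. That helps, but without a planned number and a reason for change it cannot separate thaw loss (section 12.1 gives 95% recovery) from a choice influenced by the arm.

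**Conclusion.** The point holds as a missing safeguard in an open-label trial. The plan leaves a discretionary treatment decision unfixed when the arm becomes known, and the primary outcome may depend on that decision. The freedom is widest for women aged 35 or over or with a re-transfer. A smaller freedom, one embryo or two, exists for women under 35 at a first transfer and is not included in the figures.

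Under the stated assumptions the bias is well below the planned 10-point difference. It could not produce a difference of that size alone, but at the upper end it could inflate the type I error noticeably or cost appreciable power. The figures show only what could happen: they rest wholly on assumed eligibility, imbalance and embryo effect, and are no evidence that bias occurred. The point does not call the sample size into question. It merits a modest change because the remedy is cheap.

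**What to change.** 1. On case report form page 6, above the randomisation block, add the line: *planned number of embryos to transfer (within the existing 5.4 limits)*. It is completed and signed for every woman before the arm is released. Age, transfer history and the existence of d3 frozen embryos can be established by then from the screening visit.
2. On page 7, keep the number transferred and add a reason for any departure from the planned number, for example thaw loss.
3. In section 11.2, state that planned number, actual number and departures with reasons will be reported by arm. The randomised comparison of live birth should not be replaced by one adjusted for the number actually transferred.

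The cost is one line and one reason field at existing visits; no visit or sample is added and the sample size is unchanged. Some departures will need a stated reason. The step deters and exposes choices driven by the allocation but does not eliminate them, because a departure remains possible. The clinical limits in section 5.4 are not changed.

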## 5.5 Pregnancy outcome follow-up

14 days after transfer, blood β-hCG was determined to check whether biochemical pregnancy achieved. For patients with positive hCG, sustained release vaginal progesterone gel or intramuscular progesterone, dydrogesterone and estradiol valerate were administrated continually at the same dose. 5 weeks after transfer, vaginal B-mode ultrasound examination was conducted. If gestational sac was observed, it is defined as clinical pregnancy. 6 weeks after transfer, estradiol valerate was withdrawn. 8 weeks after transfer, sustained release vaginal progesterone gel or intramuscular progesterone was withdrawn. 10 weeks after transfer, dydrogesterone was withdrawn. Letter or telephone follow-up was performed to investigate delivery and birth outcomes. For patients with negative hCG, progesterone, dydrogesterone and estradiol valerate were withdrawn.

